### Outcome measures

Data collection will be performed by a trained assessor who is blind to the patients’ assignments at baseline, after the intervention (4 weeks, 8 weeks and 12 weeks) and at the end of follow-up (24 weeks).

### Basic characteristic variables

All of the participants’ general status demographic information, such as age, sex, clinical type and GMFCS level (Gross Motor Function Classification System, GMFCS) will be obtained from baseline questionnaires.

### Primary outcome measurement

The two primary outcomes of the study—Gross Motor Function Measure (GMFM) and Fine Motor Function Measure Scale (FMFM)—will be assessed at baseline, during the intervention period (at 4 weeks, 8 weeks and 12 weeks) and in the follow-up period (at 24 weeks).

### Gross Motor Function Measure

The Gross Motor Function Measure-66 (GMFM-66) is a standardized observational instrument designed to assess the gross motor function of children with CP. It is frequently utilized in clinical and research practice to measure change over time or following interventions [24]. It allows the therapist or physician to evaluate a child’s gross motor functioning by observing the way a child performs a series of motor skills. It is divided into five sections: lying and rolling; sitting; crawling and kneeling; standing; and walking, running and jumping. Each item has a very specific detailed description whereby the evaluator scores how capable the child is of completing that item on the basis of four levels: 0 = does not initiate, 1 = initiates, 2 = partially completes, and 3 = completes or NT = not tested [25]. The total score is a summation of the scores in the five areas by the Gross Motor Ability Estimator software (GMAE Version 1.0.). In addition, the Gross Motor Ability Estimator (GMAE-2) Scoring Software for the GMFM-66 can be downloaded from the CanChild website (https://www.canchild.ca/). The greater the number of tasks attempted, the greater the accuracy is of the evaluation [25].

### Fine Motor Function Measure Scale

The Fine Motor Function Measure (FMFM) assessment scale is used to evaluate the fine motor activities of children with CP, including the upper limb activities and sensory ability. This scale includes five domains, namely audio-visual tracking ability (five items), upper limb joint’s ability (nine items), grasping ability (10 items), operation ability (13 items) and hand-eye coordination (24 items), which reflect the fine motor function by a total percentage of ability. Each item has a very specific detailed description whereby the evaluator scores how capable the child is of completing that item on the basis of four levels: 0 = does not initiate, 1 = initiates, 2 = partially completes, and 3 = completes. The total score (0~100 points) is a summation of the scores in the five areas. The higher the score is, the stronger the fine motor ability [25–27].

### Secondary outcome measures

This study has two secondary outcomes—Paediatric Evaluation of Disability Inventory (PEDI) and Cerebral Palsy Quality of Life Questionnaire for Children (CPQOL)—which will be assessed at baseline, during the intervention period (at 4 weeks, 8 weeks and 12 weeks) and in the follow-up period (at 24 weeks).

### Paediatric Evaluation of Disability Inventory

Paediatric Evaluation of Disability Inventory (PEDI) is an instrument for evaluating function in children with disabilities aged 6 months to 7.5 years. The PEDI measures functional performance and capability within the three domains of (1) self-care, (2) mobility and (3) social function in three categories, that is, the Functional Skills Scale (FSS), Caregiver Assistance Scale (CAS) and Modifications Scale. The PEDI can be administered as an interview with parents/caregivers or through observation by professionals familiar with the child. The raw scores from each domain can be converted to both normative and scaled scores. The FSS covers 40 diverse content areas assessed using 197 items scored as unable (0) or capable (1). The self-care domain comprises 73 items covering the use of utensils, personal hygiene, grooming, toileting tasks and so forth. The mobility domain has 59 items covering transfers, such as normal use of toilet/potty, getting into/out of a bed or chair and indoor and outdoor locomotion. The social function domain has 65 items covering word comprehension, communication, problem-solving, playing with adults and peers and so forth [28–30]. CAS covers 20 diverse content areas scored on the following escalating six-point scale: independent, supervision, minimal help, moderate help, maximum help and total help. The items cover the self-care domain (*n* = 8), mobility domain (*n* = 7) and social function domain (*n* = 5). The Modifications Scale measures any environmental or technical modifications needed to enhance the child’s function [31].

### Cerebral Palsy Quality of Life Questionnaire for Children

The quality of life of children with CP was measured with the Chinese version of the Cerebral Palsy Quality of Life for Children (CPQOL-Child). The cerebral palsy quality of life questionnaire for children contains 66 items in seven domains: social well-being and acceptance (SWB), functioning (FUN), participation and physical health (PART), emotional well-being (EWB), access to services (ACCESS), pain and feeling about disability (PAIN) and family health (FAMILY). Almost all of the items have the following item stem: ‘How do you think your child feels about...’ and a nine-point rating scale, where 1 = very unhappy, 3 = unhappy, 5 = neither happy nor unhappy, 7 = happy, and 9 = very happy. A few items where this stem or rating scale is not appropriate, such as items in the domain of pain and feeling about disability, have the following stem and rating scale: ‘How does your child feel about the amount of pain that they have’, where 1 = not upset at all to 9 = very upset [32, 33]. The reliability and validity of the Chinese version of the CP QOL-Child have been established.

### Safety

We will conduct the following tests on all participants at the screening stage to exclude patients with serious organic lesions: white blood cell count, platelet count, haemoglobin, coagulation function, creatinine, blood urea nitrogen, alanine aminotransferase/aspartate aminotransferase, gamma-glutamyl transpeptidase and electroencephalogram examination.

The subjects will be requested to report information about adverse events (AEs). All AEs that occur during the trial period will be recorded, such as dizziness, sweating, fainting, pallor, perturbed or chest congestion during scalp acupuncture treatment, local anaphylaxis, bleeding, unbearable prickling, local hematoma, retained needle after treatment and continuous severe local pain for more than 1 hour after acupuncture. The researcher will confirm the occurrence of AEs and record all details such as the time of occurrence, date, degree, measurement related to the acupuncture treatment and causal relationship with the acupuncture treatment. Serious AEs must be reported to the principal investigator immediately [10].

### Quality control

Before the trial, all staff members are required to attend a series of training sessions. These sessions will ensure that the personnel involved fully understand the research protocol and standard operating procedures for the study. To maintain the clinical trial at a consistently high quality, the Clinical Trial Unit of Children’s hospital affiliated with Fudan university will monitor the study documents, case report forms (CRFs), informed consent forms, serious AEs and data records regularly [10].

### Adherence

First, a WeChat group will be established for the parents of the children with cerebral palsy through which they could share their child’s rehabilitation training diary once a week using their mobile phones. Secondly, a club will be established for the parents of the children with cerebral palsy, so they can share their child’s growth experience once a month at a meeting with other parents of CP patients. These strategies hopefully will be useful in improving adherence.

### Data collection, management and monitoring

The CRF, Treatment Form and Adverse Events Form will be the first to be completed and then double-entered into the electronic data capture (EDC) system by two independent investigators, who will act as the first level of control to ensure the accuracy of the data. The second level of data integrity will include data monitoring and validation, which will be performed periodically throughout the study. The original CRFs and all other forms (including the consent forms) will be archived securely in the Clinical Trail Unit (CTU) of the Children’s Hospital affiliated with Fudan University for 5 years following publication of the last paper or report from the study [10].

The safety of the study will be monitored by a data and safety monitoring board (DSMB) of the CTU of the Children’s Hospital affiliated with Fudan University, which consists of independent clinical experts and statisticians with access to unblinded data. The DSMB is independent from the sponsor, the competing interests and the investigational site and will review the performance and safety of the trial monthly [10].

The criteria for unblinding and discontinuing allocated interventions for a given trial participant include acquiring a severe disease, having serious complications of CP or experiencing serious acupuncture-related AEs (if any), which have been described previously. The DSMB will reveal a participant’s allocated intervention and make the final decision to terminate the trial [10].

The final trial dataset will be under the custody of the Children’s Hospital affiliated with Fudan University. The data manager from the CTU of Children’s Hospital affiliated with Fudan University will have access to the complete, anonymous final dataset. Access to the final dataset or identifiable data by others will require written requests to be approved by the DSMB of the CTU of Children’s Hospital affiliated with Fudan University and all study investigators [10].

### Sample size calculation

Sample size calculations were performed based on the two primary outcomes. According to our pilot trial, we assume that, after 12 weeks of treatment, the mean change in the GMFM scores in the experimental group will be greater than the control group with a mean difference of 2.4 and a standard deviation of 3.0. At an alpha level of 0.025, 40 subjects will be required for each group to ensure a statistical power of 0.9. Assuming 20% drop out, a total of 100 participants will be needed to achieve statistical significance, so each group is required to have 50 initial participants.

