### Statistical analysis

The Statistical Product and Service Solutions (SPSS) statistical package program (version 20.0, SPSS Inc., Chicago, Ill., USA) will be used to analyse data in the CTU of Children’s Hospital affiliated with Fudan University by statisticians. All analyses, including those from any participants who drop out during the trial, will be based on the intention-to-treat (ITT) principle using the last observation carried forward rule. Missing values will be handled by the mixed model for repeated measurements. Baseline information will be collected before randomization and includes the gender and age of patients, disease course, clinical type, GMFCS level, primary outcome (GMFM, FMFM) and secondary outcomes (PEDI, CP-QOL). Descriptive statistics will be used to detail baseline participant demographics and the general status of patients, such as gender, age, disease course, clinical type and GMFCS level. Variables will be checked for normal distribution and presented as mean +/− the standard deviation and compared by Student *t* test when normally distributed. For variables not normally distributed, the data will be expressed as median +/− the interquartile range, and non-parametric tests will be used. Categorical variables will be expressed as number (%) and analysed by *χ*^2^ tests or Fisher’s exact tests, when appropriate. The mixed effect model will be used to analyse the between-group difference in repeated measures for the two primary outcomes and other outcomes (GMFM, FMFM, PEDI and CP-QOL scores) across five testing time points (weeks 0, 4, 8, 12 and 24). Mean group difference and 95% confidence intervals will be reported. Safety analyses will be compared with the incidence of AEs in the two groups using the *χ*^2^ test. A *p* value of < 0.025 will be considered as statistically significant for the two primary outcomes.

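### The sample size is said to rest on both primary outcomes but shows figures for GMFM only, and the fixed 0.025 rule, though valid, is less powerful than Holm at the same 5% family-wise error

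*Protocol article*

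**What the plan says.** The section "Primary outcome measurement" names two primary outcomes, GMFM and FMFM, each assessed at every visit from baseline to week 24.

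"Sample size calculation" opens with "Sample size calculations were performed based on the two primary outcomes". It then assumes that after 12 weeks "the mean change in the GMFM scores in the experimental group will be greater than the control group", with "mean difference of 2.4 and a standard deviation of 3.0". It concludes: "At an alpha level of 0.025, 40 subjects will be required for each group to ensure a statistical power of 0.9". A 20% dropout allowance takes this to 50 per arm, 100 in all. The section gives no difference, SD or power for FMFM, and neither does any other part of the article.

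"Statistical analysis" specifies a mixed-effects model over five time points and 95% confidence intervals for group differences. A p value below "0.025 will be considered as statistically significant for the two primary outcomes". It states no step-down or other sequential rule.

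**The concern.** There are two linked problems.

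- **The sizing statement claims more than it shows.** A reader would take the 90% power to cover both primary outcomes. The printed figures support it for GMFM only, and what the trial can detect on FMFM is undocumented.
- **The testing rule gives away power.** A fixed 0.025 for each outcome keeps the family-wise error at or below 5%. Holm keeps the same bound under any correlation between the outcomes. It tests the smaller p value at 0.025 and, if that passes, the other at 0.05. It rejects everything that the fixed rule rejects, and sometimes more.

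FMFM stands to gain most, because its power has no stated basis. A non-significant FMFM result would be hard to interpret, since nothing says what difference the trial could have seen.

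**Working it through.** **Inputs from the document** ("Sample size calculation"): difference 2.4, SD 3.0, so d = 2.4/3.0 = 0.80; alpha 0.025; power 0.90; 40 per arm; dropout 20%. Sidedness is not stated.

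**Inputs assumed:** FMFM effects from d = 0.3 to 0.8, because none is given, and a correlation of 0 to 0.7 between the two test statistics.

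**Step 1: reproduce the plan's figure.** By the normal approximation at two-sided 0.025:

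n = 2 × (2.2414 + 1.2816)² / 0.80² = 2 × 12.41 / 0.64 = 38.8, so 39 per arm.

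The t-test gives 40.07 per arm, with power 0.899 at 40. Dropout: 40/(1 − 0.20) = 50 per arm. The figure reproduces. One-sided 0.025 and two-sided 0.05 each give 33 (34 by t-test), and one-sided 0.05 gives 27. Two-sided testing is therefore inferred, because only it fits.

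**Step 2: what 40 per arm can detect on FMFM.** The detectable effect is (z for alpha + z for power) × √(2/40):

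- At 0.025: 3.523 × 0.2236 = 0.79 SD for 90% power, and 0.69 SD for 80%.
- At 0.05: 0.72 SD for 90% power, and 0.63 SD for 80%.

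**Step 3: fixed rule against Holm.** By the normal approximation, and ignoring the negligible opposite tail, FMFM power at a fixed level is Φ(d√20 − c), with c = 2.2414 at 0.025 and 1.960 at 0.05. GMFM power at 0.025 is Φ(3.578 − 2.241) = 0.909. Under Holm, FMFM gains only when its p value lies between 0.025 and 0.05 and GMFM has passed 0.025. For independent statistics:

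Holm power = P(0.025) + 0.909 × [P(0.05) − P(0.025)], where P(a) is FMFM power at level a.

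At d = 0.5: 0.498 + 0.909 × (0.609 − 0.498) = 0.599.
At d = 0.6: 0.671 + 0.909 × (0.765 − 0.671) = 0.757.

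Simulation with 1,000,000 draws per setting, at correlations 0 to 0.7, gives:

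| Assumed FMFM effect | Fixed 0.025 | Holm |
|---|---|---|
| 0.3 SD | 18% | 26–27% |
| 0.4 SD | 33% | 42–43% |
| 0.5 SD | 50% | 60–61% |
| 0.6 SD | 67% | 76% |
| 0.7 SD | 81% | 87% |
| 0.8 SD | 91% | 93–94% |

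GMFM power is 91% under the fixed rule and 91–94% under Holm. If both effects are 0.8 SD, the chance that both are significant rises from 83–86% to 90–91%.

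**Step 4: error rate.** Two independent tests at 0.025 have a family-wise error of 1 − 0.975² = 0.0494. With GMFM at 0.8 SD and FMFM null, the simulated FMFM error (correlations 0 to 0.8) was 0.025 under the fixed rule and 0.041–0.047 under Holm. Both stay within 5%.

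**The case against.** **The rule is coherent and valid.** The sizing and the analysis both use 0.025, which is a proper Bonferroni split with simple matching intervals. This stands. A reader might infer that the type I error is inflated or that N is wrong. Neither follows: the family-wise error is at most 5%, and the GMFM sample size reproduces.

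**The opening sentence may only explain the choice of 0.025, and the full protocol may hold an FMFM calculation.** Both are possible. The point is therefore not that an FMFM calculation is missing from an article, but that the article's sentence claims two outcomes while its figures cover one. Adding the FMFM inputs or narrowing the claim would settle it.

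**The size of the gain rests on assumed FMFM effects.** This stands. A reader might infer that FMFM is underpowered, but the document gives no effect or SD from which to say so. At 0.8 SD, FMFM has about 91% power under the fixed rule, and Holm adds little.

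**40 completers per arm may be too pessimistic.** The analysis keeps dropouts and uses repeated measures. With 50 per arm as an upper bound, power at 0.025 is Φ(3.0 − 2.241) = 78% for 0.6 SD and Φ(2.5 − 2.241) = 60% for 0.5 SD. The baseline may thus be higher than in the table. Holm would still add to it: the corresponding powers at 0.05, which Holm approaches when GMFM passes, are Φ(3.0 − 1.960) = 85% and Φ(2.5 − 1.960) = 71%.

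**A null FMFM result need not be misread.** The plan reports confidence intervals, which would show imprecision, and nothing says that a null would be presented as no effect. That harm is a risk of interpretation, not something the plan commits to.

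**Holm needs one test per outcome.** This also stands. No single primary time point is named for the test; week 12 appears only in the sizing assumption. Adopting Holm therefore means fixing the contrast too.

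**Conclusion.** The point holds as a mismatch in the sizing statement and an avoidable loss of efficiency. The 90% power is documented for GMFM only. For FMFM, 40 per arm gives 90% power only for an effect of about 0.8 SD at 0.025. The fixed rule is valid but is dominated by Holm at the same 5% bound. Under the assumptions used (40 analysed per arm, GMFM at 0.8 SD, two-sided tests, normal approximation), Holm adds roughly 9 to 10 percentage points of FMFM power at 0.5 to 0.6 SD and 2 to 4 points at 0.8 SD. It cannot rescue a badly undersized comparison: at 0.3 SD, FMFM power under Holm is still only 26–27%. The point should be corrected, but the trial's validity does not depend on it.

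**What to change.** Leave N unchanged, and make these changes before any unblinded outcome data are seen:

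1. **Sample size statement.** Say that the 90% power is for GMFM, and that for FMFM 40 per arm gives 90% power only for a difference of about 0.8 SD at 0.025. If FMFM pilot inputs exist, give them and the resulting power instead. State that the tests are two-sided.
2. **Testing rule.** Replace the fixed 0.025 with Holm: test the smaller p value at 0.025 and, only if it passes, the other at 0.05. If the first fails, neither outcome is significant. Apply this to one named primary contrast per outcome. Week 12, the sizing time point, is the natural choice.
3. **Intervals.** Report 97.5% intervals for both primary outcomes as the simultaneous intervals. Note that they may not match a Holm rejection at the second step. Label any 95% interval as unadjusted: a 95% interval for whichever outcome comes second is chosen by the data and does not give joint 95% coverage.

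The cost is a dated amendment to the protocol and analysis plan, a decision on the primary contrast, and slightly more involved interval reporting. No extra patients or visits are needed. Recruitment began on 1 March 2019 and the monitoring board sees unblinded data, so the amendment should be made by people without access to those data.

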### Participant recruitment

Participants will be recruited in four hospitals (Children’s Hospital of Fudan University, The 445th Hospital of Chinese People’s Liberation Army, Huajing Community Health Service Centre of Xuhui District and Jiangchuan Community Health Service Centre of Minhang District) in Shanghai, China. Prospective participants will be asked to meet with the study coordinator to discuss the study and provide information about the eligibility criteria. If children with CP are eligible and their parents/guardians are interested in participating, they will be invited for a series of rehabilitation assessments after being diagnosed by neurologists. One hundred children with CP will be included in the study. When their informed consent has been obtained, children with CP will be randomized into two groups with different treatments [10].

### Randomization and allocation concealment

The recruited patients will be randomly assigned to either the experimental group or the control group according to a randomization and allocation plan. This allocation will be done using a computer-generated, block randomization (block size of 4 and 1:1 allocation) prepared by an independent epidemiologist not otherwise involved in the trial. A computer-generated block randomization process designed by the CTU is used to allocate participants to the treatment group or the control group in a 1:1 ratio (block size = 4). The randomization list is kept strictly confidential. Allocation concealment is ensured with the use of sequentially numbered (block number and sequence number), identical, opaque, sealed envelopes. Computerized randomization preserves allocation concealment and reduces the possibility of selection bias since the research assistant is kept unaware of the group assignments until after the participants are allocated to groups.

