### Study design

This is an outcome assessor and data analyst-blinded, randomized, controlled superiority trial. The study is planned to be conducted from 1 January 2019 to 31 December 2021 in the Children’s Hospital of Fudan University. CP patients with motor dysfunction meeting the inclusion criteria will be allocated in a 1:1 ratio into either an acupuncture treatment group or a control group. CP patients in the control group will receive routine rehabilitation treatment, while the acupuncture group will receive a combination of routine rehabilitation treatment and scalp acupuncture. The Gross Motor Function Measure (GMFM) and the Fine Motor Function Measure (FMFM) will be assessed as primary outcome measures. The Paediatric Evaluation of Disability Inventory (PEDI) and the CP-Specific Quality of Life Scale (CP-QOL) will be selected as secondary outcome measurements. All assessments will be conducted at baseline, week 4 (treatment 12), week 8 (treatment 24), week 12 (treatment 36) and week 24 (follow-up). Figure 1 summarizes the flow of the entire trial. Figure 2 shows the study timeline, according to the Standard Protocol Items: Recommendations for Interventional Trials (SPIRIT) diagram. Additional file 1 presents the SPIRIT checklist.

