## Trial status

The treatment protocol version number currently in use is version 1.0, which was revised on 15 February 2019. Recruitment began on 1 March 2019, and the approximate date for the completion of recruitment will be 31 December 2021.

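### A fixed, published block size of 4, with block-labelled envelopes in a trial where treating staff are not blinded, lets some allocations be deduced: up to one third, or about 2%, depending on logistics the article does not state

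*Protocol article*

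**What the plan says.** All references are to the protocol article.

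- **Randomization and allocation concealment.** The list is "computer-generated, block randomization (block size of 4 and 1:1 allocation"), and the same section repeats that the CTU's process will "allocate participants to the treatment group or the control group in a 1:1 ratio (block size = 4"). No other block size is mentioned. The envelopes are "sequentially numbered (block number and sequence number), identical, opaque, sealed envelopes". The other safeguards are a confidential list, preparation by an independent epidemiologist, and that "the research assistant is kept unaware of the group assignments until after the participants are allocated to groups". The section treats concealment as secured by these means.
- **Study design.** "This is an outcome assessor and data analyst-blinded, randomized, controlled superiority trial". The control arm has routine rehabilitation and the other arm has the same plus scalp acupuncture. No sham is described.
- **Participant recruitment.** "Participants will be recruited in four hospitals". Prospective participants meet the study coordinator.
- **Front matter and Trial status.** The article was published on 6 January 2020. Recruitment began on 1 March 2019 and "the approximate date for the completion of recruitment will be 31 December 2021".

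**The concern.** Concealment needs two things: the next allocation must be hidden, and it must not be deducible from past ones. The envelopes deal with the first. The second is weak here for three reasons.

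- **Past allocations are visible.** Open-label is not the article's term. It follows from blinding only assessors and analysts and from comparing needling with no needling.
- **The block size is constant and public.** It appeared in print with about 24 of the 34 recruitment months still to run.
- **The label shows the block boundaries.** A block number and a sequence number tell whoever handles the envelopes where each block starts and ends.

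A recruiter who can foresee the next arm could choose whom to approach, or when to randomise, in the light of it. Under Statistical analysis, Gross Motor Function Measure (GMFM), Fine Motor Function Measure (FMFM) and gross motor classification level are recorded before randomisation, so severity may be known before the envelope is opened. Accrual of 100 children over 34 months is about 3 a month across all sites, so the last three allocations are easy to remember. Selection at entry would act before any outcome is measured, so blinded assessment would not correct it.

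**Working it through.** The article gives no predictability figure, so there is none to reproduce.

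**Inputs.** Block size 4, 1:1 allocation (Randomization and allocation concealment); four sites (Participant recruitment); 100 children (Sample size calculation).

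**Case A: the recruiter sees every earlier allocation in the block and knows its boundaries.** A balanced block of 4 has 4!/(2!·2!) = 6 equally likely orders. An assignment is certain once one arm has used both its places.

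| Position in block | P(certain) | P(best guess right) |
|---|---|---|
| 1 | 0 | 1/2 |
| 2 | 0 | 2/3 |
| 3 | 1/3 (first two match) | 1/3 × 1 + 2/3 × 1/2 = 2/3 |
| 4 | 1 | 1 |
| Sum | 4/3 = 1.33 | 17/6 = 2.83 |
| Sum ÷ 4 | **0.333** | **0.708** |

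Of 100 children on one list, 100 × 1/3 ≈ 33 assignments are certain. If each of four sites had its own list of 25 (six full blocks and one child over), the count is 4 × 6 × 4/3 = 32.

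**Case B: one list shared by four sites** (assumptions: equal and random recruitment across sites, each recruiter seeing only their own site's allocations). An earlier child in the block belongs to the same site with probability 1/4.

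- Position 3 is certain if both earlier children were at the same site and match: (1/4)² × 1/3 = 1/48.
- Position 4 is certain if all three earlier children were at the same site, (1/4)³ = 1/64, or if exactly two were and they match, 3 × (1/4)² × (3/4) × 1/3 = 3/64. The total is 4/64 = 1/16.
- Average over four positions: (0 + 0 + 1/48 + 1/16) / 4 = **1/48 ≈ 2.1%**. A simulation gave 2.1%. The best guess is then right about 55% of the time.

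With two sites instead of four, the same simulation gives about 8%, so the result depends heavily on how much of the block a recruiter sees.

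**Would a larger fixed block be enough?** Full enumeration as in Case A gives 25% certain for a known block of 6 and 20% for 8. Size alone helps only a little; it is the recruiter's knowledge of the block size that matters.

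**Illustration of consequence (assumption, not from the article).** Suppose foreseen acupuncture children would improve d GMFM points more than foreseen controls for reasons unrelated to treatment. If this happens only on certain assignments, the bias is d times the certain share. For d from 1 to 3, Case A gives 0.33 to 1.0 points, or 14% to 42% of the planned difference of 2.4. Case B gives 0.02 to 0.06 points, or about 1% to 3%.

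**The case against.** **The third is an upper bound. This stands.** It needs a recruiter who knows the block size and boundaries and has seen each earlier allocation in the block. The article does not say who opens the envelopes, whether whole blocks are held at each site, or whether enrolling staff learn earlier allocations. A reader might infer that a third of assignments are in fact known in advance; the text does not support that. The coordinator is mentioned in the singular, and the Adherence section plans a shared parents' chat group and monthly meetings. Both make wider knowledge of allocations possible, but neither establishes it.

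**Concealment is weakened, not undone. This also stands.** The independent preparation, confidential list and opaque sealed envelopes still hide contents. The first place in a block cannot be foreseen, the second is never certain, and the third is certain only one time in three.

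**Baseline is measured before randomisation and week 0 is in the mixed model. This stands in part.** Imbalance in measured GMFM or FMFM would be visible. Selection on unmeasured features, such as family support, would not be.

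**Stratification by centre.** A reader might also infer that the article is at fault for not naming it. A condensed article can leave list structure to the full protocol, so its silence is no finding. The two complaints also pull apart. The full third at every site needs whole blocks per site, which would keep each centre's arms within 2 of each other. Poor balance within centres needs a shared list, where predictability is lowest unless sites pool what they know.

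**Conclusion.** The point holds in limited form. With a fixed, published block of 4, block-labelled envelopes and unblinded treating staff, the listed safeguards do not ensure concealment, because later allocations in a block can be deduced from earlier ones. The certain share runs from about 2% (one shared list, four equal sites, each recruiter seeing only their own) to one third (whole block seen). The best-guess success rate runs from about 55% to 71%. The article does not allow a choice between these ends.

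This is an avoidable opening for selection at enrolment that could reach both primary outcomes. It is not evidence that selection has occurred or that either outcome is biased. The arithmetic is exact under each stated scenario; the uncertainty lies in which scenario describes the trial.

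**What to change.** For all participants not yet randomised, the CTU should issue a new list with randomly varying block sizes that are not disclosed to sites or published until recruitment ends. Preferably the CTU releases each allocation centrally, once consent and baseline assessments are recorded. If envelopes are kept, they should be numbered consecutively with no block number.

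The varying sizes or the central release do the real work. Removing the block label alone changes little while blocks stay at a known 4, since consecutive numbers then give away the boundaries. Taking the block size out of site documents cannot withdraw a figure already in print.

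The cost is a new list and a short amendment; the CTU already designs the randomisation process. Arm imbalance at the end of recruitment may be slightly larger: a list that stops inside a block can be out by at most half the block size, which is 2 now and would be 3 if the largest block were 6.
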